#### Other assessments

The Mini-international neuropsychiatric interview (MINI [57]), a structured interview for classifying DSM-IV and DSM 5 disorders, is used to assess whether the criteria for a Major Depressive Episode have been met. Other psychiatric classifications are also assessed during the interview. The psychometric qualities of the MINI have been reported to be good.

A record is made for all patients of whether they are using medication at the start of treatment and whether there are any changes in the prescribed medication during the 8-week treatment period.

### Statistical analysis

#### Establishing non-inferiority

The study compares the effectiveness of two forms of treatment (SPSP and CBT). The primary dependent variable is the average post-treatment score for the two groups on the IDS-SR. An ANCOVA with treatment type received as a fixed effect and baseline depression scores measured on the IDS-SR as a covariate will be performed to calculate the mean and 95% CI of the difference between the groups at the final time point on the IDS-SR. This analysis forms the basis for demonstrating that SPSP reduces depressive symptoms at least as effectively as CBT. If the lower limit of the 95% CI is above the non-inferiority limit of − 5 on the IDS-SR, it will be assumed that SPSP is not inferior to CBT. Non-inferiority analysis will be performed on the basis of both per protocol and intention-to-treat analysis.

Additional multilevel repeated measures will be used to further analyse changes in depressive symptoms and the other secondary outcome measures (functional impairment and positive mental health) and to examine possible differences between both treatment groups over time. If there are significant differences between groups in medication use or other potentially confounding variables, these variables will be included as covariates.

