## Methods

### Design

Patient inclusion for this study began in September 2016. The study is a large RCT involving the direct comparison of two treatments (Short-term Psychodynamic Structured Psychotherapy; SPSP; and Cognitive Behavioural Therapy; CBT). Before the eight-week period of the first phase of treatment, subjects are randomly assigned 1:1 to two groups and are offered 16 twice-weekly sessions of SPSP or CBT. In the second part of the study, patients who respond inadequately to treatment (defined by < 50% improvement on a depression severity scale) are randomly assigned 1:1:1 to one of three conditions: 1. continuing the initial treatment with the same therapist (control group), 2. continuing the initial treatment with another therapist, and 3. a switch of method *and* therapist; for a maximum of another 16 twice-weekly sessions. A participant flowchart is presented in Fig. 1. At baseline, patients complete several questionnaires that assess potential predictive factors. During the treatment, patients are asked to complete questionnaires about depressive symptoms, the working alliance and perceived therapist characteristics at several time points. In case of response, patients are asked to fill in follow-up questionnaires in week four and eight after completing treatment phase one. An overview of measures at different time points can be found in Table 1.

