### Power and sample size calculation

To calculate the required sample size for the first phase of the study we used the original dataset provided by the authors of a similar study which was conducted in a similar setting and population [19]. We expected this to be the best data available to make an accurate estimate of the standard deviation of the primary outcome needed to calculate the sample size.

The primary outcome measure of the current study is the severity of depressive symptoms as measured by the IDS-SR [52]. To test whether SPSP is in fact (as hypothesised) not inferior to CBT, a treatment that has already proven to be effective for treating MDD, we used the same non-inferiority margin (the maximum allowed difference in the mean outcome scores between the treatment groups to conclude that SPSP is indeed non-inferior to CBT) for continuous measures as Driessen et al. [19, 53] Accordingly, we adopted a non-inferiority margin of five points on the mean score on the IDS-SR immediately after treatment. This margin of a five-point difference between SPSP and CBT corresponds to a Cohen’s d of .30, which we assume to be a clinically acceptable difference. Power analysis for continuous outcomes [54] indicated that, to prove that SPSP is not inferior to CBT, 268 patients in total are needed for the first part of the study to provide 80% power in order to demonstrate that the lower limit of the one-sided 95% confidence interval (CI) will be above the non-inferiority limit of − 5 for the IDS-SR (1-β = 80%, SD = 16.42). Given the observed dropout rate of around 15% for the first 100 included patients, the aim is to include 308 patients for the performance of the per-protocol analysis.

Assuming that approximately 52% of the patients will be classified as non-responder after the first phase of study [4], we estimate that around 139 patients can be randomized across the three groups (1. same therapist, same treatment, 2. a switch of therapist only, 3. a switch of therapist and treatment) in the second phase of the study. According to a sensitivity analysis, by means of an analysis of covariance (ANCOVA), this suggests that we can significantly (α = .05) demonstrate a medium to large effect size (f = 0.35) with 80% power between the three groups in the second phase of the study.

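### The primary ANCOVA groups patients by treatment received, which contradicts the intention-to-treat analysis it is meant to serve

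*Protocol article*

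**What the plan says.** Under Statistical analysis, Establishing non-inferiority, the protocol article specifies a single model: "An ANCOVA with treatment type received as a fixed effect and baseline depression scores measured on the IDS-SR as a covariate". It makes this model the basis of the non-inferiority conclusion. The paragraph ends: "Non-inferiority analysis will be performed on the basis of both per protocol and intention-to-treat analysis".

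The article gives no second model, and nowhere states that allocation governs the grouping in the intention-to-treat analysis. Under Design, "subjects are randomly assigned 1:1 to two groups and are offered 16 twice-weekly sessions of SPSP or CBT". A change of therapy method is described only for phase 2, after the week-8 primary outcome.

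Under Power and sample size calculation, the recruitment target is tied to the per-protocol set: "the aim is to include 308 patients for the performance of the per-protocol analysis".

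**The concern.** An intention-to-treat analysis compares patients as randomised, whatever they went on to receive. A factor that records the therapy received does something else. A patient allocated to SPSP who was given CBT would be counted under CBT, and a patient who started neither therapy would have no value of the factor. One paragraph therefore asks for two incompatible things, and an analyst who followed the model sentence to the letter would not produce the analysis named at the end of it.

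The primary conclusion is at stake. A per-protocol set is selected after randomisation, so the intention-to-treat analysis is the only planned non-inferiority comparison that keeps the randomised groups intact. If it also groups by receipt, neither does. Patients who leave their assigned therapy may well differ in prognosis from those who stay, and moving them between arms can shift the estimate towards or away from non-inferiority.

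**Working it through.** **1. The plan's own figure.** The inputs come from Power and sample size calculation: "we adopted a non-inferiority margin of five points on the mean score on the IDS-SR immediately after treatment"; "1-β = 80%, SD = 16.42"; and the criterion that "the lower limit of the one-sided 95% confidence interval (CI) will be above the non-inferiority limit", which is a one-sided alpha of 0.05. With a true difference of zero:

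n per arm = 2 × (1.645 + 0.842)² × 16.42² / 5² ≈ 133.4, rounded up to 134, so 268 in total.

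This matches the stated 268. How the grouping factor is defined does not enter the formula, so correcting it leaves the number unchanged.

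**2. When the two groupings differ.** They differ only if some patients get the other therapy, or none, before week 8. The article gives no rate for either, so everything below is assumed and shows direction and range only.

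**3. Shift in the estimate, no true difference.** Let a fraction k of the SPSP arm receive CBT instead, let those patients score g points higher (worse) on the IDS-SR than the SPSP patients who stay, and let nobody move the other way. Compared with grouping by allocation:

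- the SPSP mean falls by kg;
- the CBT mean rises by kg(1 − k)/(1 + k);
- the SPSP-minus-CBT difference in raw scores therefore changes by −kg − kg(1 − k)/(1 + k) = −2kg/(1 + k).

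| k | g | Shift (points) | Share of 5-point margin |
|---|---|---|---|
| 0 | any | 0 | 0% |
| 3% | 8 | −0.48/1.03 = −0.47 | 9% |
| 5% | 12 | −1.20/1.05 = −1.14 | 23% |
| 10% | 16 | −3.20/1.10 = −2.91 | 58% |

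On sign: a higher IDS-SR score is worse, so a negative shift in raw SPSP minus CBT favours SPSP. The plan's limit of −5 implies a difference oriented the other way, with negative values meaning that SPSP is worse. On that scale the same shift is positive and moves the interval away from the limit.

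Other patterns behave differently. One-way switching from CBT to SPSP by worse-prognosis patients reverses the sign, as does switching from SPSP by better-prognosis patients (g negative). Equal switching in both directions with the same g cancels.

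**4. Effect on the error rate.** A simulation used 134 per arm, SD 16.42, a true SPSP deficit of exactly 5, one-sided alpha 0.05, unadjusted means, one-way switching from SPSP to CBT with g = 8, and 6,000 runs per scenario.

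| Switching | Estimated deficit, by allocation | Estimated deficit, by receipt | False non-inferiority, by allocation | False non-inferiority, by receipt |
|---|---|---|---|---|
| 0% | 4.99 | 4.99 | 0.052 | 0.052 |
| 2% | 4.98 | 4.56 | 0.050 | 0.079 |
| 5% | 5.02 | 4.01 | 0.052 | 0.127 |
| 10% | 5.01 | 3.13 | 0.048 | 0.237 |

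The closed form with a true deficit of 5, (5 − 2kg)/(1 + k), gives 4.59, 4.00 and 3.09 for 2%, 5% and 10%, in line with the simulated deficits by receipt.

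**The case against.** The best defence is that the word is loose and the intent is sound. The plan names an intention-to-treat analysis outright. The section on the Personalised Advantage Index uses the verb receive for what chance assignment gave a patient in phase one, which can only mean randomisation. The model paragraph itself speaks of a difference between groups, and Design forms those groups by random assignment. No phase 1 crossover is described, and without it the two groupings give the same answer. The size of the bias rests wholly on assumed one-way switching by patients with a worse prognosis; 8 to 16 points is about 0.5 to 1.0 of the stated SD of 16.42.

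Most of this stands, and it limits the point. A reader might infer that the trial's intention-to-treat analysis is in fact an as-treated one. The article does not support that: it would be so only if the wording were followed literally.

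A reader might also infer that the intention-to-treat set is really a completer set, because the ANCOVA uses the final time point and because of the sentence "Given the observed dropout rate of around 15% for the first 100 included patients". That does not follow either. Handling of missing week-8 scores may be left to an analysis plan that is not shown. The article does not say whether dropout means leaving therapy or lacking a week-8 score, and the questionnaires are completed online, so a patient who stops therapy could still supply one.

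The defence does not remove the contradiction. The phase 2 model uses a neutral grouping term, while the primary model specifies receipt. Nor is departure from allocation far-fetched: under Treatment integrity, therapists must complete courses in both therapies before treating study patients, and under Randomisation patients learn their condition only when therapy starts. A primary model should not leave its grouping variable to be guessed.

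**Conclusion.** The point holds as a contradiction in the wording of the primary analysis. The factor is defined by receipt, one of the two named analyses requires allocation, and nothing else in the article settles which applies.

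The numerical consequence is conditional. It is zero if every patient receives the allocated therapy in phase 1. Under the assumed one-way switching of 3% to 10% with a prognosis gap of 8 to 16 points, it is about 0.5 to 2.9 IDS-SR points in favour of SPSP, or 9% to 58% of the margin. These figures show what the wording could permit; they do not estimate bias in this trial, and other switching patterns could cancel or reverse the shift. Because the sentence governs the main conclusion, it should be corrected before the analysis is run.

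**What to change.** In Establishing non-inferiority, define the ANCOVA fixed effect for the intention-to-treat analysis as treatment as randomised (SPSP or CBT), with baseline IDS-SR as covariate as now. Use receipt of, or adherence to, the allocated therapy only to define who belongs to the per-protocol set.

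The cost is one line of text. No new data are needed, and the 268 evaluable patients and the margin stay as they are. Replacing the ANCOVA with a week-8 contrast from a repeated-measures model is a separate choice of method and is not needed to resolve this point.

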#### Treatment integrity

About 40 therapists are expected to take part in the study. The exact number will depend on various circumstances such as the time it takes to include all patients and the therapists turnover rate in the locations. The minimum requirement to participate as a therapist in the study is a master’s degree in medicine or psychology. Therapists cannot start treating patients included in the study until they have received a three-day course in SPSP and a three-day course in CBT for depression that are given by qualified and experienced experts. Audio recordings are made of every treatment session to ensure and measure treatment integrity. Recordings are discussed in the presence of peers during supervision that is given by trained supervisors every 2 weeks. Training and supervision sessions for SPSP are therefore based on the Handbook of Short-Term Psychoanalytic Supportive Psychotherapy [60]. CBT training is also based on an existing Dutch CBT protocol [63]. There is no scale for measuring treatment integrity for SPSP and within this study we will develop and test an instrument that measures the most important method specific elements of SPSP, namely adequate psychoanalytic support and the different levels of discourse. Adherence in CBT was measured with the Cognitive Therapy and Adherence Scale (CTACS) [95]. The CTACS measures competence as well as adherence for CBT in general. It has been extensively studied in patients suffering from cocaine dependence but was designed and is appropriate for measuring both competence and adherence for all types of CBT. It has good internal reliability and acceptable interrater reliability [95]. The criterion validity of the scale is high [96, 97]. In the current study, the applicability of the CTACS will be studied specifically for depressed patients.

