We therefore intend to implement a pragmatic, methodically strong, study in which the naturalistic setting will contribute to the generalisability of the results to everyday practice. This is a challenging undertaking and it also has certain limitations. Due to the naturalistic setting, for instance, it is not possible to control completely for the use of medication, although the use of medication is monitored and, if necessary, statistically controlled for in the analysis. Different treatment options for depression are available in the treatment centres and patients can choose a different kind of treatment offered by the treatment centre and refused to participate in the research project. This may result in a bias. Secondly, a double-blind design is never possible in a psychotherapy study because the therapist and patient are obviously aware of the kind of treatment that is being administered. However, by digitalising the administration of all the questionnaires that are used, both researchers and therapists are blinded to all patient-reported results and researchers are blinded to the treatment conditions. Thirdly, in spite of the fact that we include several potential predictors, one possible mediator and several moderators, there will certainly be important factors (latent and otherwise) that are not assessed in the current study. Lastly, because the study is primarily powered for the non-inferiority phase, it is expected that phase two of the study only has sufficient power to detect medium to large differences between the groups. Despite this relatively limited power, we still expect this phase of the study will generate meaningful observations on the effects of therapist and treatment switching.

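### The non-inferiority ANCOVA is specified by treatment received, which, read literally, contradicts the intention-to-treat analysis it is meant to serve

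*Protocol article*

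**What the plan says.** All references are to the protocol article.

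- **Model** (Establishing non-inferiority): "An ANCOVA with treatment type received as a fixed effect and baseline depression scores measured on the IDS-SR as a covariate will be performed". The section calls this analysis the basis for the claim about SPSP.
- **Analysis sets** (same section): "Non-inferiority analysis will be performed on the basis of both per protocol and intention-to-treat analysis". No second model or factor is given for either set.
- **Sizing** (Power and sample size calculation): "the aim is to include 308 patients for the performance of the per-protocol analysis".
- **Margin** (same section): "we adopted a non-inferiority margin of five points on the mean score on the IDS-SR immediately after treatment".
- **Decision rule**: the power section requires that "the lower limit of the one-sided 95% confidence interval (CI) will be above the non-inferiority limit". The analysis section uses the model "to calculate the mean and 95% CI of the difference between the groups at the final time point on the IDS-SR" and does not say whether that interval is one- or two-sided.
- **Therapists** (Treatment integrity): none may treat study patients "until they have received a three-day course in SPSP and a three-day course in CBT for depression". The Discussion adds that most are expected to be more experienced in CBT.

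**The concern.** Intention to treat compares the arms as randomised; a factor of treatment received does not. In a per-protocol set of patients who had their allocated therapy, the two factors coincide and the wording does no harm. In the intention-to-treat set they part for every patient who had the other therapy, and such a patient would be counted in the arm not assigned.

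The trial is sized for the per-protocol analysis, so intention to treat is the one planned non-inferiority analysis that would keep the randomised comparison intact. Coded by treatment received, it would not. Crossover is at least possible, because every therapist is trained in both methods. It could also be lopsided, because CBT is the more familiar method to most of them.

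This is not a detail left for an analysis plan to supply. The article states the factor, and the factor does not fit one of the two analyses it names.

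**Working it through.** **1. The plan's own sample size.** Inputs from the power section: margin 5, SD 16.42, one-sided 5%, power 80%, true difference 0.

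n per arm = 2 × 16.42² × (1.645 + 0.842)² / 5² = 2 × 269.62 × 6.185 / 25 = 133.4, so 134 per arm and 268 in total, as stated. The formula does not depend on how the group factor is labelled.

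**2. What the received factor does.** Let d be the CBT mean minus the SPSP mean, so that negative values are worse for SPSP and the limit is −5. Suppose a share p of the SPSP arm moves to CBT, outcomes follow the therapy received, and the movers' baseline-adjusted score is g points worse than their arm's average.

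- The group that received SPSP has mean prognosis −pg/(1−p).
- The group that received CBT has mean prognosis +pg/(1+p).
- d therefore shifts by pg/(1+p) + pg/(1−p) = 2pg/(1−p²), in favour of SPSP when g > 0.
- If g = 0 the shift is zero. If the movers go from CBT to SPSP the sign flips. With equal p and g in both directions the shifts cancel.
- By assigned arm there is no selection, but a 5-point effect of the therapies is diluted to −5(1−p) for one-way and −5(1−2p) for equal two-way switching.

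Example with p = 0.10, an assumed baseline–outcome correlation of 0.5, and movers taken as the worst 10% on a latent score correlated 0.5 with the residual. Residual SD = 16.42 × √0.75 = 14.22. The mean of the top 10% of a standard normal is 0.1755/0.10 = 1.755. So g = 0.5 × 1.755 × 14.22 = 12.48, the shift is 2 × 0.10 × 12.48 / 0.99 = 2.52, and d = −2.48. In the reverse direction d = −7.52.

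**3. Simulation.** 154 per arm (308/2), SD 16.42, true deficit 5 points, correlation 0.5, 6,000 trials per scenario, pass if the lower limit of a two-sided 95% interval exceeds −5 (nominal 2.5%). The switching rates and selection strengths are assumptions; the article gives none.

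| Scenario | Received: mean d | Received: pass | Assigned: mean d | Assigned: pass |
|---|---|---|---|---|
| No switching | −4.98 | 2.6% | −4.98 | 2.6% |
| SPSP to CBT 5/10/15%, random | −5.01/−4.99/−5.01 | 2.5/2.6/2.5% | −4.75/−4.48/−4.26 | 3.8/5.0/6.8% |
| Same, selection 0.3 | −4.10/−3.55/−3.00 | 8.0/14.7/22.5% | −4.74/−4.52/−4.28 | 3.9/5.0/6.5% |
| Same, selection 0.5 | −3.50/−2.58/−1.63 | 14.9/31.6/54.2% | −4.75/−4.54/−4.24 | 3.8/4.6/7.0% |
| 10% both ways, random or equally selective | −5.04 to −4.98 | 2.2–2.7% | −4.08 to −3.99 | 8.5–9.1% |
| CBT to SPSP 10%, selection 0.5 | −7.45 | about 0% | −4.50 | 4.9% |

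The simulated means agree with step 2; 15 of 154 moved in the 10% rows, slightly under 10%. With a one-sided 95% limit (nominal 5%) the levels rise but the pattern stays. For example, 10% switching with selection 0.5 gives 45.6% by treatment received, and random 10% switching gives 5.2%.

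**4. A different meaning of the 5-point deficit.** If the deficit is fixed between the assigned arms and movers keep the SPSP effect, analysis by assigned arm stays at 2.3–2.9%. By treatment received the pass rate is 3.8–5.8% with random and 10–68% with selective one-way switching. If movers instead take on the CBT effect while the assigned-arm difference is held at −5, random switching makes the received estimate stricter: −5/(1 − 0.10) = −5.56 at 10%.

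**The case against.** The strongest reply is that *received* simply means allocated here. The section itself names intention to treat. The Design section defines the groups by random assignment. The section on predictive and prescriptive factors speaks of patients getting a phase-one method by chance, which can only refer to randomisation. This stands as a plausible reading, but the article does not settle it.

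The second reply is that no crossover is described. The only planned switch is the re-randomisation of non-responders, after the primary time point. Sessions are recorded and supervised every two weeks, and therapists do not see IDS-SR scores during phase one, although they may still act on clinical judgement. The Discussion remark that "Different treatment options for depression are available in the treatment centres" concerns patients who decline to take part, so it is not evidence of crossover among those enrolled. All of this stands. Nor does the article say how a patient who had both therapies would be classed.

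A reader might infer that the intention-to-treat analysis is certainly an as-treated one and will pass an SPSP that truly lies at the margin. The documents do not support that. It needs crossover, mainly from SPSP to CBT and tied to poor prognosis. Under balanced switching with outcomes following the therapy received, it is the assigned-arm analysis that passes too often.

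**Conclusion.** The inconsistency is in the text and concerns the primary analysis: one model, with a factor that does not fit intention to treat, is applied to both sets. Its practical effect is conditional. With no phase-one crossover it is nil. With crossover the direction depends on who moves and which way. Selective moves from SPSP to CBT favour SPSP. Where outcomes follow the therapy received, random or balanced switching gives no bias and selective moves from CBT to SPSP count against SPSP. The simulated percentages show direction under assumed rates, selection and correlation; none is an estimate for this trial.

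The per-protocol comparison is the same under either label. That assumes the per-protocol set holds only patients who had their allocated therapy, which the article does not spell out. This is a correction of wording to make before analysis, not a demonstrated inflation of the false-pass rate.

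**What to change.** Under Establishing non-inferiority, name the treatment arm as randomised as the fixed effect for the intention-to-treat ANCOVA. If an analysis by treatment received is wanted, label it supplementary and give it no role in the non-inferiority decision. If *received* was meant as allocated, the same edit serves as a clarification.

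The cost is one line of text. The sample size stays at 268 (308 with dropout), no data collection changes, and the per-protocol result is not affected. Nothing is lost except any weight an as-treated estimate might have had in the decision.

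### The sample size assumes a one-sided 95% limit, but the primary decision rule uses an unqualified 95% CI, so the type I error is not fixed and the stated 80% power holds under only one reading

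*Protocol article*

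**What the plan says.** The Protocol article describes the primary non-inferiority test in two places.

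- **Power and sample size calculation.** The margin is set as follows: "we adopted a non-inferiority margin of five points on the mean score on the IDS-SR immediately after treatment". The section states that "268 patients in total are needed for the first part of the study to provide 80% power", and the aim is to "demonstrate that the lower limit of the one-sided 95% confidence interval (CI) will be above the non-inferiority limit" of −5. The inputs are given as "1-β = 80%, SD = 16.42". The section adds that about 15% of the first 100 patients dropped out and that 308 are to be included.
- **Establishing non-inferiority.** An ANCOVA with the baseline IDS-SR score as covariate "will be performed to calculate the mean and 95% CI of the difference between the groups at the final time point on the IDS-SR". The rule follows: "If the lower limit of the 95% CI is above the non-inferiority limit" of −5, SPSP is taken to be non-inferior. It is to be applied to both the per-protocol and the intention-to-treat analysis.

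Only the sizing section says one-sided. The analysis section mentions a 95% CI twice and gives no sidedness either time. Nothing elsewhere in the article links the two.

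**The concern.** A 95% CI reported with a mean difference is normally two-sided, and that is what standard ANCOVA output prints. Its lower limit corresponds to a one-sided test at 2.5%, whereas the limit used for sizing corresponds to 5%. The primary test therefore carries two possible error rates.

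There are two consequences. First, an analyst who follows the analysis section in its usual sense runs a test with less power than the article states. Second, there is a band of results for which one section declares non-inferiority and the other does not. If the choice is still open when the data are seen, the verdict on the primary objective can depend on it. This is not detail that an article would leave to a fuller document, because the rule is stated twice and in different terms.

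**Working it through.** **Inputs.** From Power and sample size calculation: margin 5, SD 16.42, power 80%, total 268, target 308, dropout about 15%. From Randomisation: 1:1 allocation. The true difference is not stated; I assume 0, and the assumption is supported because it returns the plan's figure. As a consistency check, 5/16.42 = 0.3045, in line with the statement that the margin "corresponds to a Cohen’s d of .30".

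**Step 1: reproduce the plan's figure.** n per arm = 2 × (z_α + 0.8416)² × 16.42² / 5².

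| Rule | z_α | n per arm | Total |
|---|---|---|---|
| One-sided 95% limit (α = 5%) | 1.645 | 133.35, so 134 | 268 |
| Two-sided 95% CI (one-sided α = 2.5%) | 1.960 | 169.29, so 170 | 340 |

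The stated 268 belongs to the one-sided 5% rule and not to the other.

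**Step 2: power under each reading, unadjusted.** SE = 16.42 × √(4/N); power = Φ(5/SE − z_α).

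| N analysed | SE | One-sided 95% limit | Two-sided 95% CI |
|---|---|---|---|
| 268 (planned evaluable) | 2.006 | 80.2% | 70.3% |
| 262 (308 × 0.85 = 261.8) | 2.029 | 79.4% | 69.3% |
| 308 (all analysed, no missing data) | 1.871 | 84.8% | 76.2% |

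A noncentral-t calculation at N = 268 gives 80.0% and 70.0%.

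**Step 3: where the verdicts differ.** At N = 268, taking negative values as unfavourable to SPSP (as the limit of −5 implies), the estimate must exceed:

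- one-sided 95% limit: −5 + 1.645 × 2.006 = −1.70
- two-sided 95% CI: −5 + 1.960 × 2.006 = −1.07

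An estimate between about −1.70 and −1.07 passes under the sizing section and fails under the analysis section read as two-sided. If the treatments are truly equal, the chance of landing there is 80.2% − 70.3% = 9.9%.

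**Step 4: effect of the baseline covariate.** With correlation r between baseline and post-treatment scores, the SD becomes 16.42 × √(1 − r²). The article gives no r, so the values below are assumptions. N = 268, two-sided 95% CI:

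| r | 0 | 0.3 | 0.4 | 0.5 |
|---|---|---|---|---|
| Power | 70.3% | 74.3% | 77.6% | 82.1% |

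Power of 80% at 268 needs r = √(1 − 268/338.6) = 0.46, where 338.6 = 2 × 169.29. With all 308 analysed it needs r = √(1 − 308/338.6) = 0.30.

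**The case against.** The best defence is that the analysis section is shorthand. It uses the same limit of −5 and looks only at the lower bound, so a reader could carry over the one-sided interval already defined in the sizing section. On that reading the power is as stated. This is possible, and the article never says two-sided. A reader might infer that the plan has fixed a two-sided rule and that its true power is 70%; the text does not support so flat a claim. What stands is that the rule is ambiguous, and that its usual reading does not match the sizing.

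A second objection is that 70% describes an unadjusted comparison, while the planned analysis is an ANCOVA. This also stands in part: 70.3% is the figure at r = 0 for 268 patients, and the covariate or a complete intention-to-treat set would raise it. However, the sizing takes no credit for the covariate and gives no correlation, so recovery to 80% is not shown.

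Two further inferences should be avoided:

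- The roughly 30% (1 − 0.703) is not the chance of wrongly concluding non-inferiority. It is the chance of failing to show it when the treatments are equal. The chance of a false conclusion at the margin is 2.5% or 5%, and the two-sided rule makes it smaller.
- The 268 is not miscalculated; it reproduces exactly. The fault is inconsistent specification.

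**Conclusion.** The concern holds as an inconsistency in the primary decision rule. The sizing fixes one-sided alpha at 5%; the analysis section, as conventionally read, fixes it at 2.5%; nothing reconciles them. If the two-sided reading is followed, the chance of missing non-inferiority under true equality is up to about 30% rather than 20%. On the protocol's unadjusted basis, power is below 80% at each of the three sample sizes examined. If the one-sided reading was intended, the 80% at 268 stands and the fault is an ambiguous rule. These figures rest on SD 16.42, a true difference of 0 and no credit for the baseline covariate. The point should be settled, because a plausible range of results would get opposite verdicts on the first objective.

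**What to change.** State one interval in both sections before unblinding. Either:

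- **(a)** in Establishing non-inferiority, specify the lower limit of the one-sided 95% CI, equal to the lower limit of the two-sided 90% CI, and declare alpha as one-sided 5%. The stated 80% at 268 then holds; or
- **(b)** in Establishing non-inferiority, specify a two-sided 95% CI, and restate the power in the sizing section as about 70% unadjusted at 268 evaluable patients. Show any gain from the ANCOVA separately, under a stated correlation assumption.

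The cost is a sentence or two of text and no extra patients. Under (b) the stated power becomes less favourable. For reference, holding 80% unadjusted power under (b) would take 340 evaluable patients, or 340/0.85 = 400 recruited at 15% dropout; the fix does not require this.
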